##### Teachers’ and students’ perception about the suitability and the development of physically active classes and active breaks

2.4.2.6

To gather information about the development of the intervention and gain insights into perceptions, barriers, areas for improvement, strengths, training needs, and sustainability, individual interviews and focus groups are conducted with teachers and students (52). Both individual interviews and focus groups are led by the same member of the research team in each study province.

Teachers involved in the PAL sessions (three teachers in Cadiz and three teachers in Caceres), as well as an equivalent sample of teachers in AB group, participate in one-hour semi-structured individual interviews. These interviews provide an opportunity for teachers to share their experiences, thoughts, and suggestions regarding the PAL and AB. In addition, a one-hour focus group is conducted with a sub-sample of six students from each class in both the AB and PAL groups. These focus groups allow students to express their perceptions, experiences, and opinions about the intervention, providing valuable insights into their engagement, enjoyment, and perceived benefits of the PAL and AB.

#### Confounding variables

2.4.3

##### Dietary patterns

2.4.3.1

Adherence to the Mediterranean diet is assessed using the updated version 2.0, previously validated in children and adolescents of the of the KIDMED questionnaire (53). The KIDMED 2.0. questionnaire consists of 16 questions that participants answer. The questions in the questionnaire have both positive and negative connotations in relation to the Mediterranean diet. Participants receive a score based on the sum of their responses, and the scores are classified into three levels: (i) ≥8, optimal Mediterranean diet; (ii) =4–7, improvement needed to adjust intake to Mediterranean patterns; (iii) ≤3, very low diet quality.

##### Sociodemographic characteristics

2.4.3.2

Sociodemographic characteristics, specifically the socioeconomic status of the participants, are collected using the Spanish-adapted version III of The Family Affluence Scale (FAS III) (54), which has been presented as a valid instrument to measure the socioeconomic status of adolescent (54). This scale consists of six questions that participants have to answer related to the purchasing power of the participant’s family. Each question is scored on a categorical scale, and the sum of the scores from the six items result in an aggregate index ranging from 0 to 13. An overall view of the different measures at different time points is depicted in Supplementary material.

### Data analysis

2.5

Data will be presented as mean and standard deviation or median and interquartile range, if applicable, for continuous variables, and frequency and percentage for categorical variables. As a cross-sectional fashion, descriptive, correlational, regression and differential analyses will be implemented. Before to implement the main analysis to test the effects of the interventions, we will test for group equivalence at baseline, by using independent samples *t*-test for continuous variables and chi square test for categorical indicators. To assess the effects of the two interventions on outcomes, repeated measured analysis will be used with the outcome measures as dependent variables in separate models, the intervention as an independent variable and controlling for potential confounders (i.e., gender). If normality analyses show non-normal distributions, the equivalent non-parametric analyses will be performed. Quantitative analyses will be completed using the SPSS 26 statistical package (IBM, Armonk, NY, USA), establishing a confidence level of 95% (*p* < 0.05).

On the other hand, the qualitative information from the semi-structured interview and the focus group will be transcribed and analyzed with the NVIVO software (55). These data will be analyzed following content analysis strategies where two phases will be differentiated. A first deductive phase aimed at detecting any type of information related to the purpose of the study. Subsequently, an inductive phase where the experiences, thoughts and reflections of teachers and students related to the AB and PAL will be identified (56).

All the analyses will be carried out considering intention to treat, keeping the participants in the group they were originally allocated and taking into consideration the CONSORT guidelines for cluster RCTs (57).

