**Methods:**

A randomized controlled study is conducted with a total of 292 students aged 12–14 years old from six schools (7th and 8th grade) in Spain (three in Cadiz and three in Caceres). One school from each study provinces is randomly assigned to either the active break intervention group, the physically active learning intervention group, or the control group. The interventions have a duration of 16 weeks. Nine main measurement categories are assessed: PA and sedentary time, health-related physical fitness, academic indicators, cognition, psychological health, motivational variables, dietary patterns, sociodemographic characteristics, as well as qualitative information through semi-structured individual interviews and focus groups. Three independent measurements of evaluation are distinguished: pre-intervention, post-intervention (week 16) and retention measurement (4 weeks after the intervention). For quantitative variables, descriptive, correlational, regression and repeated measures ANOVA will be applied.

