### Study design

2.1

The ACTIVE CLASS study is a RCT, with randomization at school level [Clinicaltrials.gov (NCT05891054)]. An intervention is developed in two experimental groups (AB intervention and PAL intervention), with pre- and post-intervention measures. Additionally, a follow-up measure is conducted 4 weeks after the intervention to assess the sustainability of the intervention program.

ACTIVE CLASS is a multicenter study whose management is designed to ensure effective collaboration and communication between research groups. The research groups consist of qualified researchers and graduates in PA and sport sciences from two Universities (University of Cadiz and University of Extremadura, Spain). Both Research groups adhere to a common study protocol for training, fieldwork, data collection and management, and quality control procedures. There is continuous telematic contact during the development of the study. In addition, each research group has responsible investigators who manage the day-to-day running of the study in their centers and are in continuous contact with their counterparts at the other university to make decisions on aspects that require a quick response or do not require a meeting of all the in researchers.

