### Participants and inclusion criteria

2.2

Participants in the ACTIVE CLASS study are apparently healthy adolescents from secondary schools in the provinces of Cadiz and Caceres (Spain). The schools included in the study are public secondary schools located in areas with a predominantly medium socioeconomic level (31). The ACTIVE CLASS study establishes the following inclusion criteria:

- *Participants’ inclusion criteria for adolescents’ students:* (i) studying 7th or 8th grade (12–14 years old); (ii) not having a physical disability or health problem that could limit PA levels.- *Schools’ inclusion criteria:* (i) having a minimum of 60 students in 7th and 8th grade; (ii) not participating in any other PA or health promotion program; (iii) Be located within a radius of 15 kilometers of the research group’s work centers in Cadiz and Caceres.

Figure 1 illustrates the flow diagram of the participants recruitment process. A total of 20 schools in Caceres and 64 schools in Cadiz are invited to participate through a letter of invitation addressed to the school’s management. A meeting is held with the management teams of the schools that accept the invitation, to explain the study and obtain their consent. From the total number of schools which accept to participate and provide their consent (three schools, both in Cadiz and Caceres), a randomization process at school level is conducted in each study province. Thus, three study groups are established in each city (Cadiz and Caceres): (i) AB intervention group, (ii) PAL intervention group, and (iii) control group. All students in the 7th or 8th grade of the participating schools who give their informed consent are invited to participate in the study. The parents of the students receive an information document describing the study, the inclusion criteria, the informed consent process, and an invitation to attend an information meeting at the school. To participate in the study, the parents or guardians must sign the informed consent form, along with the student’s consent.

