**Figure 1 fig1:**
[figure not shown]
Follow diagram of study participants.

A total of 292 participants were included in the study, ensuring effect sizes of 0.1 with an alpha level of 0.05 and a power of 0.80, even with an experimental dropout rate of 25% (GPower 3.1.9.4, Düsseldorf, Germany).

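### Schools are randomised, two per arm, but the stated repeated-measures ANOVA has no school term, so its error rates are too high if students' changes correlate within school

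*Protocol article*

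**What the plan says.** **Randomisation.** Study design (2.1): "The ACTIVE CLASS study is a RCT, with randomization at school level". Participants and inclusion criteria (2.2) adds that "a randomization process at school level is conducted in each study province". The abstract gives the counts: students come "from six schools (7th and 8th grade) in Spain (three in Cadiz and three in Caceres", and "One school from each study provinces is randomly assigned to either the active break intervention group", the physically active learning group or the control group. That makes six schools, two per arm. The text under Figure 1 gives the size: "A total of 292 participants were included in the study".

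**Analysis.** Data analysis (2.5) states that "repeated measured analysis will be used with the outcome measures as dependent variables in separate models, the intervention as an independent variable", controlling for potential confounders, of which gender is the only example. The abstract names the method: "descriptive, correlational, regression and repeated measures ANOVA will be applied". The software is SPSS 26 and the threshold is p < 0.05.

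**Clustering.** The only mention in the analysis section is its last sentence, which says that all analyses follow intention to treat, "taking into consideration the CONSORT guidelines for cluster RCTs". The article contains no school or province term, school-level summary, cluster-robust error, ICC or design effect. The baseline t-tests and chi-square tests, and the non-parametric fallback, name no cluster method either.

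**The concern.** The unit of randomisation is missing from the stated model. Students in one school share teachers, timetable and test days, so their changes over the 16 weeks may move together. A student-level analysis counts each student as independent evidence about the arm.

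After the planned 25% dropout, a student-level comparison of change between arms has about 219 − 3 = 216 error degrees of freedom (df). The design supplies 6 − 3 = 3 between-school df, or 2 once province is fitted.

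The same model serves every quantitative outcome, including physical activity and sedentary time, which are primary. A change particular to one school could therefore be reported as an intervention effect, with p-values and intervals that look more certain than the design allows.

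**Working it through.** **1. The plan's own figure.** The article says that 292 students secure 80% power for an effect size of 0.1 at alpha 0.05 with 25% dropout. It names neither the test nor the correlation between occasions, so 292 cannot be pinned down. Taking 0.1 as Cohen's f, the closest reading is the group-by-time test with 3 arms, 3 occasions and correlation 0.5:
- It needs 204 students, or 204/0.75 = 272 with dropout.
- With 219 completers its power is 0.837, so the claim of at least 0.80 is met on that reading.
- A correlation of 0.46 gives exactly 292.

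None of these variants contains a clustering allowance.

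**2. Inputs.**
- From the article: 6 schools, 2 per arm, 3 occasions, alpha 0.05, 292 students (292/6 = 48.7 per school), and 219 after 25% dropout (36.5 per school).
- Assumed: the ICC of change (0.01, 0.02, 0.05), two-sided pairwise tests and within-student correlation 0.5.

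The relevant ICC is that of change (school-by-time), because a constant difference between schools cancels from the group-by-time test.

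**3. Formulas.** With m students per school:
- Design effect: DE = 1 + (m − 1) × ICC.
- True size of a pairwise test: 2 × [1 − Φ(1.96/√DE)].
- True size of the group-by-time F test (4 numerator df): P(χ²₄ > 9.488/DE).

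**4. Results at m = 36.5.**

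| ICC of change | DE | True SE / stated SE | Pairwise size | Group-by-time size |
|---|---|---|---|---|
| 0 | 1.00 | 1.00 | 5% | 5% |
| 0.01 | 1.355 | 1.16 | 9.2% | 13.6% |
| 0.02 | 1.71 | 1.31 | 13.4% | 23.6% |
| 0.05 | 2.775 | 1.67 | 23.9% | 49.0% |

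For example, at ICC 0.02: DE = 1 + 35.5 × 0.02 = 1.71; 1.96/√1.71 = 1.50; 2 × [1 − Φ(1.50)] = 0.134.

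**5. Simulation check.** Trials were simulated with no true effect: 6 schools × 36 students, 3 occasions, F on (4, 426) df. Over separate runs the group-by-time test rejected in 13–15%, 23–24% and 48–50% of trials at the three ICCs. The pairwise contrast of change rejected in 8–9%, 14% and 23–25%. At ICC 0 both were near 5%. With no dropout (48.7 per school) the formulas give higher figures: 17%, 30% and 59% for the F test, and 11%, 16% and 29% pairwise.

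**6. A valid comparator.** An F test on school-mean changes with 2 and 3 df held its level (4.9% to 5.7% in simulation). Its power for f = 0.1 on pre–post change with all 292 students uses noncentrality λ = 292 × 2 × 0.01/0.5/DE = 11.68/DE:

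| ICC of change | 0 | 0.01 | 0.02 | 0.05 | 0.10 |
|---|---|---|---|---|---|
| Power | 0.43 | 0.32 | 0.25 | 0.17 | 0.12 |

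If province takes one df, the two-sided critical t rises from 3.18 (3 df) to 4.30 (2 df). With the same λ, power is about 0.29 at ICC 0 and 0.10 at ICC 0.10.

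**The case against.** The strongest reply is that the authors know the trial is clustered. The CONSORT sentence covers all analyses, section 2.5 speaks of repeated-measures analysis (a family that includes mixed models), ANOVA is named only in the abstract, gender is given as an example, and a fuller analysis plan may exist. Part of this stands: a reader might infer that the final analysis will certainly ignore school, and the documents do not show that. But the article does not leave the model open. It names the dependent variable, factor, example covariate, software and threshold, and a reporting guideline is not a method. What remains is an acknowledgement of clustering that is not carried into the stated model.

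A reader might also infer that repeated-measures ANOVA cannot accommodate school. It can: school nested in arm, with school-by-time as the error stratum, would do so. The fault is that no such term is specified.

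A third tempting inference is that adding any school term cures the problem. A random school intercept alone leaves school-by-time variation in the residual. A mixed model is not a safe equivalent of the school-means analysis either. In simulation of pre–post change with six schools, the school variance was estimated as zero in 29–53% of trials at ICCs of 0.01 to 0.05. With error df then reverting to the student level, the arm test rejected in about 8–10% of trials at ICCs of 0.02 to 0.05.

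**Conclusion.** The point holds as a defect in the stated analysis: schools are randomised and the named model omits them. How much that matters depends on an ICC of change that the documents do not give. Over 0.01 to 0.05 with 36 students per school, the false-positive rate runs from about 13–15% to 48–50% for the group-by-time test, and from about 8–9% to 23–25% for a pairwise contrast.

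Two stronger statements are not supported. One is that error rates are several times 5% as a matter of fact: at an ICC of 0 there is no inflation, and at 0.01 the pairwise rate is a little under double. The other is that any drift within a school would be declared an effect: even at 0.05 about three quarters of pairwise tests would not reject. The error may also be small for some outcomes. Because the model governs every quantitative outcome and the remedy is wording and code, it should be put right before effects are analysed.

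**What to change.** Replace the stated effect model, in one explicit sentence that also gives content to the CONSORT reference:
- **Primary inference:** a two-stage analysis of covariate-adjusted school-mean changes, with province as block and a t or F reference on the between-school df (3, or 2 with province fitted).
- **Report** the ICC of change for each outcome.
- **Supporting analysis only:** a mixed model with student, school and school-by-time effects, with df held at the between-school level even when the school variance is estimated as zero.
- **Avoid** student-level df, and sandwich errors with six clusters. No effectiveness claim should rest on a student-level p-value.

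The cost is analysis wording and re-coding, with no new data. The price in precision is real: intervals become much wider, and the school-level test has power of about 0.43 at best for f = 0.1. The change corrects the error rate but cannot give two schools per arm adequate power. The article should state this limit and restrict its effectiveness claims to match.

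### A normality check can replace the covariate-adjusted repeated-measures model with an unnamed non-parametric analysis that, with the usual SPSS tests, loses the adjustment and may lose the group-by-time comparison

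*Protocol article*

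**What the plan says.** Under Data analysis, the article commits to one effect analysis for every outcome: "repeated measured analysis will be used with the outcome measures as dependent variables in separate models", with "the intervention as an independent variable and controlling for potential confounders (i.e., gender"). The abstract's Methods paragraph names the technique: "descriptive, correlational, regression and repeated measures ANOVA will be applied".

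The design behind that model is fixed elsewhere:
- Three arms: "three study groups are established in each city (Cadiz and Caceres").
- Three occasions: "pre-intervention, post-intervention (week 16) and retention measurement (4 weeks after the intervention").
- Allocation by school: "The ACTIVE CLASS study is a RCT, with randomization at school level".

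The next sentence of Data analysis gives the fallback: "If normality analyses show non-normal distributions, the equivalent non-parametric analyses will be performed". It names no normality test, threshold or replacement analysis. It does not say whether raw outcomes or model residuals are examined, or whether the arms are pooled. The software is SPSS 26. Accelerometer-measured activity and sedentary time are the primary outcomes, and the fallback sentence does not exempt them.

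**The concern.** The sentence is a decision rule. If it is followed as written, the test that carries the trial's conclusion is chosen after the data are seen, separately for each outcome.

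The replacement may also answer a different question. The trial asks whether change over time differs between arms, adjusted for stated confounders. The rank tests an analyst would normally reach for in SPSS compare either arms or occasions. An outcome that triggers the rule would lose its planned adjustment for gender. It could also lose the between-arm comparison of change.

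Many outcomes are candidates: five-point items (the fitness scale, self-rated health), Likert scale scores, three-level EQ-5D items and observed on-task behaviour. Some outcomes would then be analysed with the adjusted model and others without it, and the results could not be compared across the paper.

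**Working it through.** The plan gives no figure for this rule, so there is none to reproduce. The stated sample size is used only to set realistic sample sizes.

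**Inputs from the article.** 292 students; 25% dropout; 3 arms; 3 occasions; significance level 0.05.
- Completers: 292 × 0.75 = 219.
- Completers per arm: 219 / 3 = 73.

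**Step 1. What each usual rank test keeps.**

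| Analysis | Compares arms | Compares occasions | Group-by-time | Covariate |
|---|---|---|---|---|
| Planned repeated-measures model | yes | yes | yes (implied by the design) | yes |
| Kruskal-Wallis or Mann-Whitney at one occasion | yes | no | no | no |
| Kruskal-Wallis or Mann-Whitney on change scores | yes | through the change | yes, one change at a time | no |
| Friedman or Wilcoxon within an arm | no | yes | no | no |

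No rank test in the table keeps the covariate. Only the change-score version keeps a between-arm contrast of change.

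**Step 2. What goes wrong with Friedman by arm.** Simulation of 2000 trials, 3 × 73 students, 3 occasions. Assumed: within-student correlation 0.5, no intervention effect, no school effect, and a time shift of 0.25 SD common to all arms.
- Per-arm Friedman tests disagree (significant in some arms, not in others): 74% of trials.
- Mixed-ANOVA group-by-time test rejects: 5.6%, close to its nominal 5%.

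A formula explains the first figure. If each arm's test rejects independently with probability p, the chance that the three arms disagree is 1 − p³ − (1 − p)³ = 3p(1 − p). Setting 3p(1 − p) = 0.74 gives p(1 − p) = 0.247, so p is about 0.44 or 0.56. The maximum, at p = 0.5, is 3 × 0.25 = 75%, so the assumed shift is close to the worst case. With no time shift, p = 0.05 and disagreement is 3 × 0.05 × 0.95 = 14%, still well above 5%.

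**Step 3. Kruskal-Wallis on change scores.** Same simulation frame. Null rejection is 0.05. With a 0.3 SD effect in one arm, power is 0.44, against 0.46 for the ANOVA interaction. This version is sound as a contrast of change, but it is unadjusted.

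**Step 4. How often the rule would fire.** Shapiro-Wilk at 0.05, 1000 runs, assumed skewed distributions:

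| Shape | n = 73 (one arm of completers) | n = 292 (all students) |
|---|---|---|
| Skewness 0.5 | 32% | 89% |
| Skewness 0.7 | 57% | 99.6% |
| Skewness 1 | 87% | 100% |
| Five-point item | 100% | 100% |

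At n = 219 with gamma data, rejection is 67% at skewness 0.45, 93% at 0.63 and about 100% at 0.89. The same distribution can therefore pass or fail depending only on whether arms are pooled, and the article does not settle that.

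**The case against.** Four stronger readings are tempting, and the article does not support them.

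- **That no non-parametric equivalent exists.** This is too absolute. Rank methods for factorial longitudinal data exist, as do rank-transformed models, and Step 3 shows that a rank test on change scores keeps the between-arm contrast with little loss of power. Since the article names no test, it cannot be said that Friedman or single-occasion Kruskal-Wallis would be used.
- **That the switch discards the clustering.** The main model as written names no school term, so the switch has none to remove. Clustering enters only through a general reference to the CONSORT guidance for cluster trials, which covers all analyses, the fallback included. In simulation with an assumed school-by-time variance of 0.02 and no effect, false-positive rates were 40% for the mixed ANOVA without a school term, 26% for Kruskal-Wallis on change and 15% on post scores. The switch did not worsen that error. The missing school term is a separate and larger matter.
- **That the rule tests raw outcomes rather than residuals.** The text does not say which. This is an ambiguity.
- **That the switch is near-certain for moderately skewed outcomes.** This holds for pooled samples under the assumed distributions. It fails for checks made by arm, at 32% and 57%. The 100% figure is for a five-point item, where leaving the normal model is reasonable.

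It is also fair to say that an article may leave the exact fallback test to a fuller plan, and that the group-by-time test is implied here and not spelled out. Both points stand. Neither rescues the rule: the data-driven replacement of the main analysis is stated in the text, and naming a test later would not make the choice independent of the data.

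**Conclusion.** The point holds in a limited form. The article fixes a normality-triggered switch, outcome by outcome and with no exception for the primary outcome, from the covariate-adjusted repeated-measures model to an unnamed alternative. The usual SPSS rank tests would lose the adjustment for gender in every case, and would lose the group-by-time comparison unless change scores are used.

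The size depends on which test replaces the model. With change scores, the loss is mainly the covariate. With Friedman by arm, spurious disagreement between arms runs from 14% (no time shift) to a ceiling of 75%, and is 74% at the assumed 0.25 SD common shift. The trigger rate runs from 32% to 100% across the sample sizes and shapes in Step 4. The distributions, the normality test, the within-student correlation and the time shift are all assumptions; the article gives none of them. This should be corrected, but it does not by itself invalidate the trial.

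**What to change.** Delete the switching sentence and state instead:
- The prespecified repeated-measures model (group, time, group-by-time, stated covariates) is the primary analysis for every continuous outcome, whatever a normality test shows.
- Non-normality is judged on model residuals.
- Where residuals are clearly non-normal, one named sensitivity analysis is reported beside the primary result: a log or square-root transformation, or a rank analysis of change scores labelled as unadjusted.
- Single ordinal items (self-rated health, EQ-5D levels) use an ordinal model, and on-task proportions a binomial model, both specified in advance.

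The cost is a few lines of analysis text and a little more modelling. Ordinal and binomial effects will be reported on a different scale from the continuous outcomes. This change does not deal with the absence of a school term, which needs its own correction.

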##### Physical activity and sedentary time

2.4.1.1

Actigraph (Actigraph GT3X+, Inc., Pensacola, FL, USA) is used to measure PA and sedentary time. Participants wear the monitor for eight consecutive days. To ensure a higher compliance rate when wearing the device, it was decided that participants would wear it on the non-dominant wrist, as this is an area that has been shown to be just as valid as on the waist (34). Participants are instructed to wear the accelerometer throughout the day (including sleeping hours), except for aquatic or situations where the device may come into contact with water. Sleep duration is captured through self-reported data, wherein each participant is provided with an accelerometer diary. Participants are required to diligently record the times at which they initiate sleep and awaken each day while wearing the accelerometer.

The screening and data collection procedures are conducted following the established protocols used in previous studies involving adolescents (34). Data will be downloaded and analyzed by using the ACTILIFE software (v.6.11.7 Actigraph TM). Inclusion criteria for the analyses are: (i) at least 3 days of valid weekday data and at least 1 day of valid weekend data; (ii) a minimum of 10 h of recording per day (34, 35).

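### Repeated measures ANOVA, run as named and without imputation, is a complete-case analysis for each outcome and does not deliver an analysis of all allocated students

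*Protocol article*

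**What the plan says.** The abstract (Methods) names the method: "For quantitative variables, descriptive, correlational, regression and repeated measures ANOVA will be applied". It also sets the number of waves: "Three independent measurements of evaluation are distinguished: pre-intervention, post-intervention (week 16) and retention measurement", the last taken 4 weeks after the intervention.

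Section 2.5 (Data analysis) is looser: "repeated measured analysis will be used with the outcome measures as dependent variables in separate models". It adds a normality check with a non-parametric fallback, and SPSS 26 as the software. It also declares: "All the analyses will be carried out considering intention to treat, keeping the participants in the group they were originally allocated", with a reference to the CONSORT guidance for cluster trials.

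Two other places bear on missing data. Section 2.2 says that 292 participants secure the stated power "even with an experimental dropout rate of 25" per cent. Section 2.4.1.1 admits an accelerometer recording to analysis only with "at least 3 days of valid weekday data and at least 1 day of valid weekend data" and at least 10 hours of recording per day.

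**The concern.** Classical repeated measures ANOVA, as in the SPSS repeated measures procedure, needs a complete row for each student: one value at every wave in the model. A student with valid baseline and week-16 values but no valid value at the retention wave leaves the model altogether, and the observed week-16 value goes too. The usual non-parametric repeated measures tests have the same requirement, so the fallback in section 2.5 does not help.

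Two things are at stake. The first is precision, because data collected at the time point of most interest may be thrown away. The second is the population analysed. A plan that invokes intention to treat would be expected to use the data of all allocated students, whereas this method uses those complete at every wave. If completeness relates to activity, motivation or arm, the comparison could be biased.

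**Working it through.** **Inputs from the article.** N = 292; effect size 0.1; alpha 0.05; power 0.80; dropout 25% (section 2.2); three groups and three waves (abstract).

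**Assumptions, because the article does not give them.** The effect size is Cohen's f. The test is the group-by-time interaction. Sphericity holds. The correlation between waves, rho, is 0.5, with 0.3 and 0.7 as the range. Clustering by school is ignored throughout.

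**Formula.** Noncentral F with k groups and m waves:

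lambda = N × f² × m / (1 − rho), df1 = (k − 1)(m − 1), df2 = (N − k)(m − 1).

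**Step 1: the plan's own figure.** After 25% loss, 292 × 0.75 = 219 students remain. With k = 3, m = 3 and rho = 0.5:

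- lambda = 219 × 0.01 × 3 / 0.5 = 13.14, df = 4 and 432, power 0.84.
- The need with equal groups is 204, or 204 / 0.75 = 272 with dropout.

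So 292 meets the stated target as a lower bound. It cannot be reproduced exactly, because the test and rho are not given. At rho = 0.3 the power at 219 is 0.68; at rho = 0.7 it is 0.98.

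**Step 2: week-16 values discarded when 25% of students lack some wave.** That is 292 × 0.25 = 73 students, who leave a three-wave model whatever the pattern. What differs is how many of them had an observed week-16 value:

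| Pattern of the 25% | Complete students | Observed week-16 values discarded |
|---|---|---|
| All leave before week 16 and do not return | 219 | 0 |
| All are missing only at the retention wave | 219 | 73 |

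**Step 3: a heavier pattern.** Suppose that baseline is complete and 25% are missing independently at each of the two follow-up waves.

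- Complete at all three waves: 292 × 0.75² = 164.
- Week-16 value observed: 292 × 0.75 = 219.
- Observed at week 16 but discarded: 219 − 164 = 55.
- At least one follow-up value: 292 × (1 − 0.25²) = 274.

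Power with 164 complete students:

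| rho | lambda | Power |
|---|---|---|
| 0.3 | 7.03 | 0.54 |
| 0.5 | 9.84 | 0.70 |
| 0.7 | 16.40 | 0.91 |

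A model that uses all available waves would keep the 219 week-16 values and draw on the 274 students with at least one follow-up value. In this step, 25% is a rate per wave, so the total share with any missing wave is 1 − 0.75² = 44%. That is more than the 25% in section 2.2 if that figure means the overall loss; the article does not say which it means.

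**The case against.** **There is no contradiction with intention to treat.** A reader might infer that the method contradicts the intention-to-treat statement. The article explains that phrase as keeping participants in their allocated group. Complete cases analysed by allocated arm satisfy that wording. This objection stands: the method falls short of an analysis of all allocated students, but it does not break the sentence.

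**Deletion is inferred.** The article nowhere states listwise deletion. Section 2.5 does not say ANOVA, its wording could cover a mixed model in SPSS, and a missing-data rule may sit in a plan that is not shown. This stands in part. The absence of a rule is not the complaint. The abstract does name repeated measures ANOVA, and the normality check with a non-parametric fallback fits that reading.

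**The sample size already allows for the loss.** A reader might infer that the trial is underpowered by its own figures. It is not on this ground: if 25% is the total share with any missing wave, 219 remain and power is about 0.84 at rho = 0.5.

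**The loss may not touch every outcome.** Models are separate by outcome, so the same students need not be lost from each. The text shown does not confirm a June accelerometer recording; the schedule by time point is in supplementary material that is not shown. If accelerometry were taken only at baseline and post-intervention, a missing retention wave could not remove a week-16 value for the primary outcome; a failed recording at baseline still would. This stands as a limit on scope.

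**Bias is not shown.** The article gives no evidence that missingness differs by arm or activity. The mixed model also relies on data being missing at random, so it would not cure missingness that depends on unobserved activity. This stands too.

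**Conclusion.** The point holds in a limited form. The method named in the abstract, run without imputation, is a complete-case analysis for each outcome. It can discard observed week-16 data and does not analyse all allocated students.

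The size is uncertain: 0 to 73 week-16 values at 25% overall loss, or about 55 with 164 complete students if 25% are missing independently at each of two follow-up waves. In that last case the nominal power of about 0.70 moves between 0.54 and 0.91 as rho goes from 0.3 to 0.7. These figures rest on assumed rho, test family and missingness pattern, and ignore clustering.

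The documents do not support reading this as a literal breach of the intention-to-treat statement, an error in the stated sample size, or a demonstrated bias. It is a weak choice of method that is cheap to improve.

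**What to change.** In the abstract and in section 2.5, replace repeated measures ANOVA and its looser equivalent with one named model: a likelihood-based linear mixed model using all available waves from all allocated students. Make arm versus control at week 16 the primary contrast. State that a recording failing the wear criterion makes only that wave missing and does not exclude the student. Keep the complete-case analysis as a sensitivity analysis.

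The cost is a change of wording and of model specification. SPSS 26, already named, can fit the model, and no further data are needed. There are two caveats. The model assumes that data are missing at random, which should be stated. And with only six schools, two per arm, any school effect in the model needs a small-sample method; the change of model does not settle that by itself.
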